#### Exploratory Outcomes

Exploratory outcomes investigate the effects of food familiarity or novelty on food choices and assess the potential of visual attentional bias data, derived from 2 well-established tools, to predict final food choices among healthy adults.

### Outcome Measures

In this study, several key metrics will be used to assess visual and neural responses to food stimuli, which are listed in Textbox 1.

Outcome measures.
**Time to first fixation (TTFF)**
The interval from the onset of the stimulus to the first fixation on the target. TFF indicates the initial orienting response towards a stimulus. A shorter TTFF suggests quicker attentional capture by the target, reflecting the efficiency of visual attention and its alignment with task-relevant stimuli [26]. This measure is crucial for understanding how quickly participants direct their gaze to familiar versus novel stimuli.
**Total fixation duration (TFD)**
The cumulative time spent fixating on a target during a given trial. TFD reflects the allocation and engagement of attention over time. A longer TFD on a target implies greater sustained attention and interest, indicating how engaging or relevant the stimulus is perceived to be. This measure elucidates how familiarity affects sustained visual attention toward different products [27].
**Reaction times (RTs)**
The time taken by participants to respond to the dot-probe after it appears, measured from the onset of the probe. RTs provide insights into attentional biases and decision-making speeds. Shorter reaction times suggest faster processing and quicker attentional shifts towards the location of the dot-probe, helping determine how stimulus familiarity influences the speed of attention allocation and the efficiency of task-related responses [15].
**Event-related potential (ERP) components**
ERP components capture the neural responses associated with processing visual stimuli. A total of 2 key components will be analyzed:P300: A positive deflection occurs approximately 300-600 milliseconds post stimulus. The P300 component is linked to attention and memory processes, reflecting the allocation of attentional resources and the processing of significant or novel stimuli. Higher P300 amplitudes suggest greater attentional engagement and relevance of the stimulus, providing insights into how product familiarity influences cognitive processing [28].N100: A negative deflection occurs approximately 100 milliseconds post stimulus. The N100 component is associated with early sensory processing and selective attention, indicating the initial detection of and orienting toward a stimulus. Variations in N100 amplitude can reveal differences in early attentional processing between familiar and unfamiliar products [29].

### Participant Timeline

The protocol was prepared according to the SPIRIT (Standard Protocol Items: Recommendations for Interventional Trials) guidelines (the SPIRIT checklist can be found in Multimedia Appendix 1) [30]. In addition, Table 1 provides an overview of the study timeline.

**Table 1 table1:** SPIRIT (Standard Protocol Items: Recommendations for Interventional Trials) report of enrollment, interventions, and assessments.

Study period		Enrolment (–t_1_)	Allocation (0)	Postallocation (t_1_)	Close-out (t_2_)
**Enrolment**					
	Eligibility screen				
	Informed consent	✓			
	Demographic data	✓			
**Interventions**					
	Allocation		✓		
	Dot-probe task			✓	
**Assessments**					
	Reaction times			✓	
	Eye-tracking metrics			✓	
	Event-related protentional components (P300, N100)			✓	
	Food choice questionnaire				✓

### Sample Size

An a priori power analysis was conducted using G Power version 3.1.9.7 (Department of Psychology, Heinrich Heine University Düsseldorf) to determine the appropriate sample size needed to achieve sufficient statistical power for our study. The analysis was designed for an *F* test, with an assumed medium effect size of *F*=0.35, a significance level of α=.05, and a desired statistical power of 0.80. Based on these parameters, the calculated sample size required was 40 participants. Specifically, the number of groups (between-subject factor) was set at 2 (500 ms vs 2000 ms), and the number of measurements (within-subject factor) included 8 (2 stimulus types [familiar or novel] across 4 food categories). In addition, the correlation among repeated measures was conservatively set at 0.5. The medium effect size was chosen based on the existing literature on attentional bias studies, which commonly report medium to large effect sizes [23]. Under these specifications, G Power estimated an achieved power of 0.820, exceeding the commonly accepted threshold of 0.80 for adequate power. This indicates that a sample size of 40 participants is sufficient to detect a medium effect size in our primary outcome using repeated measures ANOVA, ensuring the study is powered to identify meaningful changes while balancing feasibility within the constraints of a pilot study.

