### Outcomes

#### Primary Outcome

The primary outcome includes identifying the difference in 3 attentional bias metrics toward familiar or novel food stimuli at different presentation times. Detailed descriptions of these outcome measures are provided in the “Outcome Measures” section below.

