### Statistical Analysis

ERP data will be preprocessed with EEGLAB v14.1.2 toolbox for MATLAB [33], involving noise removal, epoching from stimulus onset to 1000 milliseconds post stimulus, and averaging across epochs to extract ERP components. Potentials reflecting ocular or muscle-related artifacts were removed using logistic infomax independent component analysis [34]. Further artifacts will be removed using the clean_rawdata plugin for EEGLAB.

Regarding dot-probe and electroencephalography attention-related measures (RTs, and N100 and P300 amplitudes, respectively), repeated measures ANOVA will be conducted, including the stimulus type (familiar vs novel across 4 food categories) as a within-subject factor, and group (500 ms vs 2000 ms) as a between-subject factor. Similarly, ANOVA will also be conducted to examine eye-tracking measures (TTFF, FD) between groups (500 ms vs 2000 ms). Post-hoc analyses will be conducted with Bonferroni adjustments for multiple comparisons. In addition, relationships between eye-tracking measures (TTFF, FD) and ERP components (P300 and N100 amplitudes) will be calculated by the Spearman correlation analysis. IBM SPSS Statistics 20 (IBM Corp) software will be used to analyze the data. No interim analyses are scheduled for this study.

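### The stated power of 0.820 at N=40 matches a test of 500 ms against 2000 ms averaged over all foods, not the familiar-versus-novel primary question it is said to support

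*Protocol article*

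**What the plan says.** The Sample Size section describes an F test "with an assumed medium effect size of *F*=0.35", "a significance level of α=.05, and a desired statistical power of 0.80". It says that "the number of groups (between-subject factor) was set at 2 (500 ms vs 2000 ms), and the number of measurements (within-subject factor) included 8", the 8 being two stimulus types in each of four food categories, and sets the correlation among repeated measures at 0.5. From this "the calculated sample size required was 40 participants". It then states: "Under these specifications, G Power estimated an achieved power of 0.820, exceeding the commonly accepted threshold of 0.80 for adequate power". The closing sentence of the section applies this to the primary outcome.

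The Primary Outcome section defines that outcome as "identifying the difference in 3 attentional bias metrics toward familiar or novel food stimuli at different presentation times". The hypotheses at the end of the Introduction are about familiar compared with novel items: reaction time, total fixation duration and P300 amplitude. Statistical Analysis plans a repeated-measures ANOVA for reaction time, N100 and P300, "including the stimulus type (familiar vs novel across 4 food categories) as a within-subject factor", with the presentation-time group as the between-subject factor.

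**The concern.** A two-factor repeated-measures design has three kinds of test: the between-subject main effect, the within-subject effect and their interaction. G*Power has a separate routine for each, and the same inputs give very different answers. The primary question concerns a within-subject contrast (familiar versus novel) and its interaction with duration group. If the reported power comes from the between-subject routine, it describes neither.

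What is at stake is the justification for N=40. A reader told that power is 0.82 for the primary outcome will judge a null familiarity result, or a null familiarity-by-duration result, against a figure that belongs to another effect.

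**Working it through.** **Inputs, all from Sample Size:** f=0.35 (f²=0.1225), alpha=0.05, N=40, k=2 groups, m=8 measurements, rho=0.5. An equal split of 20 per group is assumed, because the ratio is not stated.

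**1. Reproducing the plan's figure (between factors).**
λ = f²·N·m / (1+(m−1)·rho) = 0.1225×40×8 / 4.5 = 8.711, on F(1, 38).
Power = 0.8202. At N=38 it is 0.7993, so 40 is the smallest even total that reaches 0.80. Both stated figures are matched.

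**2. Same inputs, within-factor or within-by-between interaction, m=8.**
λ = f²·N·m / (1−rho) = 0.1225×40×8 / 0.5 = 78.4, on F(7, 266).
Power is above 0.999. N=10 would already give 0.88, so this routine would not have led to 40.

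**3. Familiar versus novel alone (m=2), or its interaction with group.**
λ = 0.1225×40×2 / 0.5 = 19.6, on F(1, 38). Power = 0.991, and N=20 reaches 0.80.

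**4. Other variants tried.** None gives 0.820.
- Within or interaction, m=8, lower-bound epsilon 1/7: 0.903
- SPSS-type effect size: 0.557 (m=2), 0.994 (m=8)
- Cohen-type effect size: 0.578 (m=2), 0.996 (m=8)
- Between factors, m=2: 0.702
- Single measurement: 0.578

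**5. Why the effect-size scale matters.** For a 1-df paired contrast λ = dz²·40. For a difference in bias score between two groups of 20, λ = d²·(20×20/40) = d²·10. The λ of 19.6 in step 3 therefore corresponds to dz = √(19.6/40) = 0.70 for familiarity and d = √(19.6/10) = 1.40 for familiarity by duration. If 0.35 is instead read as the standardised familiar-minus-novel difference itself (an assumption), power is 0.578. If it is read as the between-group difference in that bias (also an assumption), power is 0.190.

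**6. What N=40 can detect with 80% power.** On F(1, 38) this needs λ of about 8.265.
- Familiarity, 1 df: dz = √(8.265/40) = 0.45
- Familiarity by duration, 20 per group: d = √(8.265/10) = 0.91, in SDs of the familiar-minus-novel score

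As an illustration only, an assumed d=0.5 for the second test has power 0.338.

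**The case against.** Five points can be made for the plan.

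- **The arithmetic is right and the routine is inferred.** Both are true. The fault lies in the effect to which the figure is attached. The inference is strong, because one formula matches the power to three decimals and the sample size as well.
- **The 500 ms versus 2000 ms comparison is itself planned.** The primary outcome mentions presentation times, and Statistical Analysis plans an ANOVA between duration groups for the eye-tracking measures. This stands as far as it goes. A duration effect averaged over familiar and novel items is still not the difference between them, nor a change in that difference.
- **The study may have ample power anyway.** A reader might infer from the mislabelled figure that the study is underpowered, especially for the presentation-time part. The documents do not support that. At the plan's own f and correlation under G*Power defaults, the relevant tests have power of 0.991 or more. Low figures arise only from effect sizes or scales that the documents do not give.
- **The ANOVA may already be a 2×4 factorial.** A reader might infer that the plan uses one 8-level factor. The wording allows that but also fits separate familiarity and category factors, and the 8 in Sample Size is only a power input.
- **This is a pilot, and the limitations paragraph concedes reduced power for smaller effects.** That general caveat does not correct the specific claim in Sample Size.

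**Conclusion.** The point holds in this form: 0.820 is the power of the presentation-time main effect averaged over all eight cells, and the statement that 40 participants suffice for the primary outcome does not follow from it. The conclusion rests on the inferred routine and on an equal split of 20 per group.

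The true power for the primary question cannot be read from the protocol, because the scale of f=0.35 is not stated. For the familiarity contrast, the readings tried run from 0.557 to above 0.999. For the interaction, they run from 0.190 to above 0.999. The finding is a wrong justification, not a demonstrated shortage of participants.

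The analysis model is a secondary matter and conditional. If stimulus type were run as one 8-level factor, its 7-df test would mix differences between milk, oil, sauces and beverages with familiarity, and would not answer the primary question.

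**What to change.** **Sample Size.** State the G*Power routine, the effect tested and the scale on which 0.35 is defined. Replace the 0.820 with what N=40 gives for the primary tests: 80% power at dz=0.45 for the 1-df familiarity contrast and, with duration between subjects and 20 per group, at d=0.91 for familiarity by duration. Remove the sentence linking 0.820 to the primary outcome.

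**Statistical Analysis.** Specify familiarity (2 levels) and food category (4 levels) as separate within-subject factors. Name the 1-df familiarity effect and familiarity by duration as the tests that answer the primary question.

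The cost is two rewritten paragraphs and no added participants. The stated sensitivity for familiarity by duration will look less favourable than the present text suggests. The abstract says that data analysis has not started, so the change can still be made before results are seen.

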### Recruitment

Participant recruitment will be conducted using a multifaceted approach, combining both physical and internet-based strategies. This will include distributing flyers in community centers, libraries, and university campuses, as well as posting digital flyers on social media platforms (eg, Instagram). We will also use email invitations, university newsletters, and internet-based research recruitment platforms. Potentially eligible individuals will be identified, and members of the study team will reach out to them via phone or email to provide detailed information about the study and extend an invitation to participate. Interested individuals will be directed to complete an electronic screening survey to assess eligibility. Those who qualify and express interest will be contacted by the study team to verify screening information. During this meeting, the study team will review the study procedures, answer any questions, and go over the consent process.

### Data Collection Plan

#### Dot-Probe Task

The dot-probe task will be implemented using E-Prime 3.0 software (Psychology Software Tools, Inc) for both eye-tracking and ERP components. Each trial will commence with a 500-millisecond presentation of a fixation cross at the center of the screen. This serves to focus participants’ attention on the central point before the food stimuli are displayed. Following the fixation cross, a pair of images (one familiar and one novel) will be shown side-by-side for either 500 or 2000 milliseconds. The side on which each type of image appears is randomized to control for location bias. After the image pair is presented, a dot-probe will appear in the location previously occupied by one of the images. The dot will remain visible for 500 milliseconds. Participants will indicate the location of the dot by pressing the “L” key if the dot appears on the left side of the screen, or the “R” key if it appears on the right side. The response time and accuracy will be recorded for each trial (Figure 1).

**Figure 1 figure1:**
[figure not shown]
Schematic view of the dot-probe task design.

Each image pair will be displayed 8 times throughout the experiment, ensuring all possible dot-probe locations are tested. This results in a total of 128 trials, with varying combinations of familiar or novel images appearing in each trial. Reaction times in all trials will be recorded. RTs refer to the time it takes for participants to respond to the target stimulus by pushing the right or left key after the presentation of the stimulus. RTs are extracted as a measure of the speed at which individuals can shift their attention from the cue to the target. The inter-trial interval will be 2500 milliseconds. Reaction times of incorrect responses as well as reaction time outliers (reaction times less than 200 ms, greater than 1500 ms) will be excluded from the analyses. Temporal dynamics refer to variations in the duration of stimulus presentation. Shorter durations (eg, 500 ms) are often used to capture initial orienting responses. A quick reaction during a brief presentation may indicate a rapid attentional capture by the cue. Longer durations (eg, 2000 ms) are used to explore sustained attention and processing.

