Visual attention is an important factor in the food decision-making process, providing a key contribution to subsequent decision-making [7]. Understanding attentional bias, where individuals preferentially process specific types of information, has been critical in understanding food-related behaviors in the context of consumer behavior or etiology of diseases, namely obesity [11]. Attentional bias has been measured using novel psychophysiological methods, including eye-tracking [12]. Eye-tracking technology provides an objective way to measure eye fixation duration and movement, capturing visual attention toward prominent stimuli [13,14]. In eye-tracking, participants are presented with pictures, either concurrently with reaction- and time-based paradigms or with instructions to simply gaze at pictures presented. One well-documented reaction time paradigm is the dot-probe task. In this task, participants are presented with cues of varying duration, which impacts the interpretation of attentional bias [15]. Previous research suggested stimulus presentation lengths of ≤200 milliseconds being associated with automatic orientation of attention, whereas presentation lengths ≥500 milliseconds are associated with maintained attention [16]. Currently, there are several studies in the literature applying either eye tracking or dot-probe to investigate the attentional bias to different food or nonfood stimuli among the healthy population or across disorders, such as anxiety, obesity, and eating disorders [17-20]. While visual probe tasks are the most commonly implemented task assessing food-related attentional bias, some current evidence has called their test-retest reliability into question and suggests combining different methods of attentional bias assessment for obtaining more reliable results [21].

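### Dot-probe reaction times at 500 ms are read as initial orienting, although the cut-offs cited in the Introduction place both planned durations under maintained attention

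*Protocol article*

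**What the plan says.** All references are to the protocol article. The Introduction, summarising earlier dot-probe work, describes "stimulus presentation lengths of ≤200 milliseconds being associated with automatic orientation of attention", whereas "presentation lengths ≥500 milliseconds are associated with maintained attention". The Dot-Probe Task section specifies that each image pair "will be shown side-by-side for either 500 or 2000 milliseconds"; no shorter display is planned. After Figure 1, the same section assigns meanings to the two durations. For the brief one: "Shorter durations (eg, 500 ms) are often used to capture initial orienting responses"; it adds that a fast response after a brief display may point to rapid capture by the cue. For the long one: "Longer durations (eg, 2000 ms) are used to explore sustained attention and processing".

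Duration carries weight in the plan. The primary outcome is "identifying the difference in 3 attentional bias metrics toward familiar or novel food stimuli at different presentation times", and the Statistical Analysis section enters "group (500 ms vs 2000 ms) as a between-subject factor" in the repeated measures ANOVA of reaction times and ERP amplitudes. Separately, the Outcome Measures textbox treats time to first fixation (TTFF) as the index of the initial orienting response.

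**The concern.** The same 500 ms condition receives two meanings. Under the Introduction it belongs with maintained attention; under the Dot-Probe Task section it stands for orienting and is set against 2000 ms as the sustained-attention condition. Nothing in the article reconciles them.

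What is at stake is the interpretation of a factor in the primary outcome. If the labels after Figure 1 are carried into the report, a reaction-time bias at 500 ms could be read as rapid capture, and a difference between durations as a difference between orienting and maintenance. Neither reading follows from the cut-offs that the article cites.

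**Working it through.** **Inputs.** Cut-offs from the Introduction: 200 ms or less for automatic orienting, 500 ms or more for maintained attention. Durations from the Dot-Probe Task section: 500 and 2000 ms.

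**Durations against cut-offs.**

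| Duration | 200 ms or less? | 500 ms or more? | Class by the Introduction | Label after Figure 1 |
|---|---|---|---|---|
| 500 ms | no (500/200 = 2.5 times the limit) | yes, exactly on the inclusive boundary | maintained | initial orienting |
| 2000 ms | no | yes | maintained | sustained |

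So 0 of 2 durations fall in the orienting class and 2 of 2 in the maintained class. The labels conflict at 500 ms only.

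**Is there room for a gaze shift before the probe at 500 ms?** The Eye Tracking section counts a fixation if it starts at least 100 ms after picture onset and lasts at least 100 ms. The earliest qualifying fixation can therefore be complete at 100 + 100 = 200 ms, leaving 500 − 200 = 300 ms before the probe. Attention at probe onset need not be where it first went. This shows only that a shift is possible; the article gives no gaze latencies.

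**Which effect does the stated power refer to?** The Sample Size section gives f = 0.35, "a significance level of α=.05, and a desired statistical power of 0.80", 2 duration groups, m = 8 measurements, a correlation of 0.5 and N = 40, with achieved power 0.820.

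- Between-factors test: λ = f²·N·m / (1 + (m − 1)ρ) = 0.1225 × 40 × 8 / (1 + 7 × 0.5) = 39.2 / 4.5 = 8.71, with df (1, 38). Power is 0.8202, which reproduces the stated figure.
- Within or interaction test: λ = f²·N·m / (1 − ρ) = 39.2 / 0.5 = 78.4, with df (7, 266). Power exceeds 0.999, which does not match.

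The stated power thus belongs to the main effect of the 500 versus 2000 ms factor. This does not demonstrate the inconsistency. It shows that the factor with the disputed label is not peripheral to the design.

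**What does not depend on the label?** The textbox reads reaction time as the speed with which attention is allocated to familiar or novel items. The hypotheses in the Introduction and Discussion concern familiar versus novel for reaction time, total fixation duration and P300. None of these needs 500 ms to mean orienting.

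**The case against.** The strongest reply is that both statements are hedged background. The Introduction reports what earlier research suggested, in terms of association; the text after Figure 1 speaks of what is often done and what a fast response may indicate. Neither is a binding rule, and 500 ms sits exactly on the boundary. No hypothesis predicts a dissociation between orienting and maintenance, and the Statistical Analysis section names the groups only by their durations. This stands, and it limits the point to an unreconciled interpretation.

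A reader might infer more: that all reaction-time data at 500 ms will be wrongly interpreted, or that the study cannot separate orienting from maintenance at all. The documents do not support either. The familiar-versus-novel comparison survives whichever label is used, and misreporting is a risk rather than something the plan prescribes. TTFF is already tied to initial orienting, and the textbox also links N100 to it. N100 is a less secure basis at present, because the Electroencephalography Acquisition section starts the epoch at the dot and the Statistical Analysis section at stimulus onset.

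A reader might also infer that the Introduction is right and the Dot-Probe Task section wrong. That turns on the cited source, which is not available here. Justifying the orienting reading of 500 ms would be an equally valid resolution.

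The hedging does not remove the inconsistency: the article offers the reader two incompatible meanings for one level of a factor in the primary outcome.

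**Conclusion.** The point holds for the interpretation of the dot-probe reaction-time contrast between durations. By the article's own cited cut-offs neither duration probes orienting, so a 500 versus 2000 ms difference in reaction time should not be presented as orienting versus maintenance unless that reading is justified. The contrast can still inform on earlier versus later attention. The conclusion rests on one assumption: that the cut-offs in the Introduction are meant to apply to this task, which is the paradigm that paragraph discusses. No sample size, power figure or test statistic changes.

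**What to change.** Before analysis starts, reconcile the Introduction with the text after Figure 1 in the Dot-Probe Task section.

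- Either justify the orienting reading of 500 ms against the cited cut-offs, or describe the two reaction-time conditions as earlier versus later attention and state that their contrast does not test orienting versus maintenance.
- Base orienting claims on TTFF, in line with its definition in the Outcome Measures textbox. For eye-tracking measures the Statistical Analysis section names only the comparison between duration groups, so add the familiar-versus-novel comparison explicitly for TTFF.
- The location of the first fixation could be derived from the gaze record as supporting evidence. It is not among the measures listed in the Eye Tracking section, so it would have to be added as a derived variable.

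No new condition or data collection is needed. The timing is favourable: the Abstract states that analysis has not begun, with recruitment well advanced (36 of 40 in the Abstract, 34 in the Results section). The cost is a narrower claim for the reaction-time index and a small clarification of the TTFF analysis.
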